### **2.2.3.4 Concomitant care and interventions**

Physicians may give symptomatic medicine (i.e. ibuprofen, acetaminophen, decongestant, mucolytic) according to their usual practice and these will be recorded in the CRFs and symptom diary. Parents will record the use of these medicine in the symptom diary. The decision on concomitant medication will be made without knowledge of allocation to the prednisolone or control group.

## **2.2.4 Outcomes**

### **2.2.4.1. The pilot study outcomes**

#### **Recruitment rate**

Recruitment rate is defined as the proportion of consultations with potentially eligible children who provide their consent to be included in the study. As this is recognised as a crucial aspect of conducting a clinical trial and may cause study discontinuation due to low recruitment [37], we will assess this in our pilot study. We will identify the rates and challenges during the recruitment process and determine the best strategy for the main study to overcome these challenges and obstacles.

### ***The success of the study procedures***

The success of the study procedures includes the following: (1) obtaining informed consent from the patients and their parents; (2) the recruitment based prespecified eligibility criteria, including the use of otoscope to diagnose AOM if feasible; and (3) the stratification and randomisation process, including stratifying eligible children based on the severity and obtaining the allocation result whether the children will be allocated to the prednisolone or control group.

### ***Ability to measure planned outcomes in the main study***

We will assess the ability to measure planned outcomes in main study, which are: (1) the proportion of children with pain reduced by at least the minimum clinically important amount, at day-3 after randomisation. This will be assessed using a VAS recorded in the patient symptom diary; (2) the severity of pain and other AOM-relevant symptoms at various time points using VAS, AOM-SOS, and the symptom diary; (3) duration to AOM resolution; (4) adverse effects, defined using standard clinical trials criteria, recorded in the diary, and reported to the central office and ethics committee as required.; (5) complications of AOM (e.g. perforation of tympanic membrane(s), mastoiditis); and (6) AOM recurrence, defined as a new episode of AOM at one to three months after randomisation. We will report these narratively due to a limited sample size and insufficient formal power calculation for this pilot study to be able to detect actual effects of corticosteroids to improve clinical outcomes in AOM.

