## CHAPTER 2 – METHODS

### 2.1 Trial design

This study is a pilot of a parallel, pragmatic, stratified, randomised, open-label, single-blind controlled trial of corticosteroids, as monotherapy for mild AOM, and in addition to individually prescribed antibiotics for severe AOM. In the main study, we will stratify eligible children based on the clinical specialty (primary care or secondary/tertiary care) and severity of AOM (mild or severe). However, for this pilot study, we only include ear-nose-throat-specialists (ENTs) who work at tertiary centres for the convenience of the implementation of the mechanistic sub-study as tympanometry is only available at the hospitals (tertiary centres). Therefore, we will stratify the children based on their AOM severity and then will randomly allocate to corticosteroid (prednisolone) or control (usual care without prednisolone) (Figure 1) with the allocation ratio of 1:1. Because it is an open-label study, the parents/caregivers and an appointed nurse who will perform the randomisation will be aware of treatment allocation, whilst the clinicians and tympanometry technicians will remain unaware of the treatment.

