### 2.1.6 Sample size

We did not determine a sample size for the pilot study. There are several suggestions in calculating the sample size for a pilot study (e.g. at least 55 participants or at least 9% of the sample size of the main study) [39]. Since we will need 60 children in the mechanistic sub-study, we will include 60 children with AOM in our pilot study. The sample size of the mechanistic study was determined based on the main primary outcome, which is the mean value of static acoustic admittance or acoustic compliance in the tympanogram. In a previous study of children with middle ear effusion (MEE) who underwent tympanometry assessment and had a history of chronic or recurrent middle ear disease [40], the response within each subject group was normally distributed with standard deviation 0.3. If the true difference in the experimental and control means is 0.3 units, we will need to study 22 experimental subjects and 22 control subjects to be able to reject the null hypothesis that the population means of the experimental and control groups are equal with probability (power) 0.9. The Type I error probability associated with this test of this null hypothesis is 0.05. With a 20% allowance for dropouts, the total sample size becomes 56 or we will include 60 children for this pilot study.

Using the worst-scenario that of 50 physicians who work at seven appointed hospitals and have approximately 97 patients with AOM per week, we estimate that only 30% of the physicians will confirm their participation and 25% of the patients will give their consents to participate in our study. We then estimate that it will require nine months to recruit 60 children with AOM in this pilot study, including the extra months for potential slow recruitment and last follow-up (three months after the baseline visit).

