#### **2.4.3 Statistical methods**

For the recruitment rate, we report the outcome as the proportion of children in percentages (%). For the success of the study procedures and the ability to measure planned outcomes in main study, we will report the outcomes as the proportion of clinicians in percentages based on the grading

scale of their feedback reporting on prespecified outcome measure tools. For the compliance to study and study drug, we will report the outcomes as the proportion of children in percentages who attend the follow-up visits and complete the cycle of study drug.

To assess the verification of sample size calculation for main study, we will report this outcome as the proportion of children in each stratum (mild and severe AOM group) and those with pain at Day-3 after randomisation in the control group.

For the mechanistic sub-study, we will report continuous variables (i.e. the change in MEE at various time points (mean in days standard deviation), the duration of MEE) as a mean difference (MD) with 95% confidence intervals (CI) also the difference between two groups. We also will report the correlation between ear pain and other symptoms with the changes in MEE at various time points.

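### Six planned main-study outcomes, including adverse effects and complications, are to be reported narratively for lack of power; low power is a reason not to test, not a reason to leave out descriptive estimates and intervals

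*Protocol*

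**What the plan says.** Section 2.2.4.1, under the heading on ability to measure planned outcomes in the main study, numbers six outcomes. Items 1 to 3 are day-3 pain response on the VAS, severity of pain and other symptoms over time, and duration to resolution. The harms items are "4) adverse effects, defined using standard clinical trials criteria, recorded in the diary" and "5) complications of AOM (e.g. perforation of tympanic membrane(s), mastoiditis". Item 6 is recurrence. One reporting rule covers all six: "We will report these narratively due to a limited sample size and insufficient formal power calculation for this pilot study". The sentence goes on to say that the pilot cannot detect true effects of corticosteroids on clinical outcomes.

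Section 2.4.3 returns to this heading in these terms: "the ability to measure planned outcomes in main study, we will report the outcomes as the proportion of clinicians in percentages", according to the grades on their feedback forms. Two other results in that section bear on the point:

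- To verify the main-study sample size, it plans the proportion with pain at day 3, in the control arm only and with no interval mentioned.
- For the tympanometry sub-study, it plans mean differences with 95% confidence intervals.

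On size, section 2.1.6 says: "Since we will need 60 children in the mechanistic sub-study, we will include 60 children with AOM in our pilot study". Section 2.1 randomises children "with the allocation ratio of 1:1".

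**The concern.** The rule gives a reason, and the reason does not support it. Lack of power means that a non-significant test says little, so tests and efficacy claims should be avoided. It does not make a count, a mean, a standard deviation or a confidence interval invalid. In a small study the width of the interval is the main information a reader needs.

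Harms have most at stake. Parents and children know the allocation (2.3.2) and parents record adverse effects in the diary, while the pilot has no data monitoring committee (2.5.1). A verbal summary without numerators, denominators and limits would leave readers, and the planners of the main study, unable to see which event rates the pilot has excluded and which it has not.

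**Working it through.** **Inputs.** 60 children allocated 1:1 give 30 per arm (2.1, 2.1.6). The protocol sets no interval level or threshold for adverse events. I assume a two-sided 95% level and show the one-sided 95% limit beside it.

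**The plan's own sample size.** Section 2.1.6 states that "the response within each subject group was normally distributed with standard deviation 0.3", with a difference of 0.3, power 0.9 and type I error 0.05 (taken as two-sided).

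- n per arm = 2 × (1.960 + 1.282)² × (0.3/0.3)² = 21.0, rounded up to 22. The t-test power at 22 per arm is 0.8997.
- A one-sided test would give 18, which does not match the stated 22.
- Dropout: 22/(1 − 0.20) = 27.5, rounded up to 28 per arm, or 56 in total. This agrees with "With a 20% allowance for dropouts, the total sample size becomes 56", which the protocol then raises to 60.

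The 60 children are therefore sized for tympanometry, and the protocol is right that the clinical outcomes have no power calculation.

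**What 30 children per arm can say about an event rate.** With no events, the exact upper limit is 1 − 0.025^(1/n) two-sided and 1 − 0.05^(1/n) one-sided.

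| Events / n | Exact two-sided 95% interval | One-sided 95% upper limit |
|---|---|---|
| 0/30 | 0 to 11.6% | 9.5% |
| 1/30 | 0.1% to 17.2% | not computed |
| 2/30 | 0.8% to 22.1% | not computed |
| 3/30 | 2.1% to 26.5% | not computed |

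Other figures on the same basis:

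- Chance of seeing no event in 30: 0.90^30 = 4.2% if the true rate is 10%, and 0.95^30 = 21% if it is 5%.
- Between-arm difference with 0/30 in each arm (Newcombe 95%): −11.4 to +11.4 percentage points.
- Sensitivity: if only 24 per arm had data (30 × 0.8), the zero-event limits would be 14.2% two-sided and 11.7% one-sided. This borrows the tympanometry dropout allowance, where follow-up runs to day 90. Table 1 schedules adverse effects and complications only to day 7, so 24 is not their documented denominator.

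**The protocol's practice elsewhere.** Section 2.4.3 gives tympanometry 95% intervals in the same 60 children. Section 1.1.2 argues the safety of corticosteroids from event counts with 95% intervals in arms of similar size: vomiting in 3/41 versus 1/40, and anxiety in 9/43 versus 2/43. It also rates confidence in earlier AOM trials as low because of small samples and very wide intervals. A report without intervals would not let readers make that judgement about this pilot.

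**The case against.** The strongest reply has four parts.

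1. **Narrative reporting does not forbid numbers.** The first outcome is itself defined as a proportion, and the sentence goes on to disclaim detection of effects, which is the right caution. This stands in part: the protocol does not say that counts will be left out. But neither 2.2.4.1 nor 2.4.3 requires them.
2. **The heading concerns feasibility.** Feedback grades suit the question of whether the tools work. That is fair, but the narrative rule applies to the outcomes themselves, and the data will have been collected.
3. **A statistical analysis plan could supply the table.** It could, but it would have to be reconciled with an explicit rule and its stated reason. This is not a mere silence.
4. **Adverse events are recorded, and serious ones go to two ethics committees (2.5.2).** True, but recording and notification do not set how results by arm are presented.

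Some stronger readings are tempting, and the protocol does not support them:

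- A reader might infer that the trial yields no estimates or intervals at all. Section 2.4.3 plans both for tympanometry, and a control-arm proportion for day-3 pain.
- A reader might infer that the main study's sample-size check is lost. The two assumptions to be verified, 35% severe and 42.5% pain resolution in controls (2.2.4.1), are proportions that 2.4.3 covers. No VAS standard deviation enters the inputs shown.
- A reader might take 10% as a limit that the pilot fails to exclude. The protocol names no such threshold. With 0/30, 10% lies inside the two-sided interval but just outside the one-sided limit.
- That an absence of events would be read as reassurance is a reasonable inference, not something the protocol states.

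**Conclusion.** The concern holds for the six outcomes listed in 2.2.4.1, and for those only. An explicit reporting rule rests on a reason that justifies avoiding tests but not avoiding descriptive estimates. Section 2.4.3 does not repair it beyond one control-arm proportion.

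The size is best shown by harms: no events in 30 children leaves rates of up to 11.6% open (9.5% one-sided). This assumes that all 30 children in an arm are assessed and that the exact method is used; with fewer assessed, the limit rises. The tympanometry analysis, recruitment, compliance and sample-size verification are not affected. The defect lies in reporting, not in the design, but it should be corrected because the data are already to be collected.

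**What to change.** In 2.2.4.1, replace the narrative reporting rule with wording such as the following, and repeat it in 2.4.3:

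*Each of the six outcomes will be reported descriptively by arm: number with data, n/N or mean and SD, with 95% confidence intervals (exact limits for adverse effects and complications). Between-arm differences will be given with 95% confidence intervals and labelled descriptive. No hypothesis tests will be performed on these outcomes.*

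The caution that the pilot cannot establish effects should stay. The cost is a short wording change in two sections and one results table from case report forms and diaries already planned. The downside is that the published intervals will be wide.

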### ***The compliance to study and study drug***

The compliance to study and study drug is defined as a proportion of children who regularly take the study drug (assessed using the symptom diary and any left-over drug) and come to follow-up visits per protocol. Participants will be followed-up closely by clinicians and research staff. Children will return for a visit at day-3 after randomisation, ensuring collection of the primary outcome.

### ***The verification of sample size calculation for main study***

Based on our size calculation, we plan to enrol 760 children in the main study. We estimate that there will be 35% of the total sample of children with AOM in the severe group (i.e. children with severe symptoms, fever  $\geq 39^{\circ}\text{C}$ , children aged  $< 2$  years with bilateral AOM, AOM with perforation of tympanic membrane). Therefore, within this pilot study, we can assess the accuracy of this assumption. Also, we will check another assumption of the sample size calculation, which was the proportion in the control group with the resolution of pain at three days, which was 42.5%.

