#### 2.2.2 Eligibility criteria

##### 2.2.2.1 Inclusion criteria

We will include 60 children aged six months to 12 years old with AOM, defined as current onset (48 to 72 hours) of AOM-relevant symptoms (e.g. earache, ear tugging/rubbing or irritability in non-verbal children). If it is feasible, otoscopic findings of middle ear effusion (e.g. bulged tympanic membrane, limited or absent mobility of the tympanic membrane, air fluid level, ear discharge) and acute inflammation (e.g. erythema) will confirm the diagnosis.

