##### 2.2.2.2 Exclusion criteria

We will exclude children:

1. with major and severe medical conditions (e.g. heart diseases, kidney failure)
2. who are immunocompromised (e.g. HIV, children receiving cancer treatment)
3. with congenital malformations and/or syndromes (e.g. cleft palate, Down's syndrome)
4. with ear ventilation tube(s)

5. exposed to persons with varicella (chicken pox) or active Zoster infection in the past three weeks without prior varicella immunisation or infection
6. who have high risk of strongyloidiasis infections with symptoms and signs of unexplained eosinophilia, skin reaction due to larvae penetration into the skin (e.g. inflammation, oedema, petechiae, severe pruritus), particularly on the feet regions, pulmonary (e.g. dry cough, throat irritation, dyspnoea, wheezing, haemoptysis, repeated episodes of fever and mild pneumonitis), or gastrointestinal symptoms (e.g. upper abdominal pain, diarrhea, anorexia, nausea, epigastric pain, malabsorption, and vomiting)
7. who have taken systemic (i.e. oral, injection) or topical steroids in the preceeding four weeks
8. who have taken antibiotics in the preceeding two weeks
9. who are hypersensitive to prednisolone or prednisone, or other corticosteroids

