## **2.2.4.2. The mechanistic or tympanometry sub-study outcomes**

### **Primary outcomes**

#### ***The change in middle ear effusion (MEE) at various time points***

We will assess the change in the MEE at the following time points: baseline visit, visit-1 (day-3), visit-2 (day-7), visit-3 (day-30), and visit-4 (day-90). We will measure MEE using static acoustic admittance, defined as “the amount of energy absorbed by the tympanic membrane and middle ear, measured in mmho or mL” [38]. We will also measure the difference of this results between the intervention and control group.

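### Children with a perforated eardrum are eligible for the tympanometry sub-study, but the protocol does not separate their admittance readings, which cannot be read as effusion

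*Protocol*

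**What the plan says.** **Who is eligible.** The section on verifying the main-study sample size lists what makes a case severe, and one item is "AOM with perforation of tympanic membrane". The pilot uses this stratum. Section 2.1 says "Therefore, we will stratify the children based on their AOM severity", and the verification section says of the severe share: "We estimate that there will be 35% of the total sample of children with AOM in the severe group" and "Therefore, within this pilot study, we can assess the accuracy of this assumption". The inclusion criteria (2.2.2.1) accept discharge among the otoscopic signs that confirm effusion ("air fluid level, ear discharge"). The exclusion criteria (2.2.2.2) rule out ventilation tubes but do not mention perforation.

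**Who is measured.** The sample size section sets the mechanistic sub-study at 60 children and makes the pilot the same 60. Table 1 schedules tympanometry at baseline and on days 3, 7, 30 and 90, with otoscopy at the same visits.

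**What is measured.** The primary mechanistic outcome (2.2.4.2) is the change in effusion over these visits, measured by static acoustic admittance, which is defined as "the amount of energy absorbed by the tympanic membrane and middle ear". Section 2.4.3 reports it as a mean difference between arms with a 95% confidence interval.

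**Perforation later on.** Perforation is also an example of a complication to be recorded as a planned main-study outcome (2.2.4.1).

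**The concern.** The endpoint is defined through a system of which the eardrum is a part. When the drum is open, the instrument no longer measures that system, and the value says nothing reliable about fluid behind the drum. Such ears are eligible by design and may also arise during follow-up. No section on outcomes, enrolment, data collection or statistical methods flags them, sets them aside or assesses their effusion another way.

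Two things are at stake. First, ears perforated at baseline can add values with no treatment signal and dilute the difference between arms. Second, the outcome is a change over time. A drum that opens or heals between visits can move admittance without any change in effusion, and if prednisolone affects perforation or healing, the error differs by arm. The same readings feed the duration of effusion and its correlation with symptoms.

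**Working it through.** **Inputs from the protocol:** SD 0.3, difference 0.3, power 0.9, type I error 0.05 (sidedness not stated; two-sided reproduces the plan), 20% dropout, 60 enrolled, 1:1 allocation, severe share 35%. **Assumption:** the share *f* of children whose reading carries no treatment signal, because the protocol gives no perforation share.

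**1. The plan's own figure.** n per arm = 2(1.960 + 1.282)² × (0.3/0.3)² = 21.01, rounded up to 22. The t-test power at 22 per arm is 0.900. With dropout, 22/0.8 = 27.5, rounded up to 28 per arm, total 56. The stated 22 per arm and 56 both reproduce.

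**2. The margin.** 60 × 0.8 = 48 children, or 24 per arm, with t-test power 0.924. This is 2 per arm above the 22 required, so it absorbs an unreadable share of 1 − 22/24 = 8.3%, or 5 of 60 children.

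**3. The ceiling at baseline.** 60 × 0.35 = 21 children in the severe stratum. Perforation is one of several severe criteria, so the perforated number should be lower.

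**4. Readings kept.** A share *f* = k/60 in each arm shows no treatment effect, with the within-group SD still 0.3. The mean difference becomes 0.3(1 − f). The prednisolone arm is then a mixture with variance 0.09[1 + f(1 − f)], so the pooled SD is 0.3√[1 + f(1 − f)/2]. Power is that of a two-sided t-test with 24 per arm.

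**5. Readings set aside.** The difference stays 0.3 and the SD 0.3, with 24(1 − f) per arm.

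| k of 60 | f | Difference if kept | Pooled SD if kept | Power, kept | Per arm, set aside | Power, set aside |
|---|---|---|---|---|---|---|
| 0 | 0 | 0.300 | 0.300 | 0.92 | 24.0 | 0.92 |
| 2 | 0.033 | 0.290 | 0.302 | 0.90 | 23.2 | 0.91 |
| 6 | 0.100 | 0.270 | 0.307 | 0.85 | 21.6 | 0.89 |
| 10 | 0.167 | 0.250 | 0.310 | 0.78 | 20.0 | 0.87 |
| 21 (ceiling) | 0.350 | 0.195 | 0.317 | 0.55 | 15.6 | 0.77 |

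Simulation of the kept case gives 0.900, 0.845, 0.778 and 0.551 for 2, 6, 10 and 21 children, in line with the formula.

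In every row, setting the readings aside costs less power than keeping them. The table treats an affected child as uninformative throughout. A drum that is open at only some visits would affect only those visits. The table does not cover perforation that differs by arm, which would cause bias and cannot be sized from the protocol.

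**The case against.** The best counter-argument is that rules for invalid tympanograms usually sit in the analysis plan, the CRF or a measurement manual, none of which is shown. The physicians are ENT specialists who assess each tympanogram before recording it. Otoscopic and tympanometric results go on the same outcome form, so drum status may already be captured.

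Part of this stands. A reader might infer that readings from perforated ears will certainly be averaged in as ordinary values. The documents do not say so; they are silent, and specialist review might catch such readings. A reader might also take the exclusion of ventilation tubes as proof that the authors saw the problem for tubes and missed it for perforation. No reason for that exclusion is given, so it shows nothing of the kind. The admittance definition does not use the word intact either; that an open drum invalidates the reading is reasoning about the measurement, applied to the protocol's definition.

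What does not stand is that this is only analysis detail. Eligibility, the primary measure and the schedule of data collection are fixed in the protocol, and together they apply the measure to ears in which it does not show effusion. A later analysis plan can set such readings aside only if drum status is tied to each tympanogram. Nothing in the text requires that, and sections 2.2.2.1 and 2.4.1 make otoscopy conditional on feasibility although Table 1 schedules it.

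**Conclusion.** The point holds as one of measurement validity. Eligible children include some whose primary reading cannot be interpreted as effusion, and the protocol as written does not distinguish those readings.

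Its size is unknown. A reader might conclude that the sub-study is underpowered, but the documents do not support that. The sample size arithmetic is right, 21 of 60 is a ceiling at baseline, and with 2 affected children power stays at about 0.90, the design target. At 6 and 10 children it would be about 0.85 and 0.78 with readings kept, against 0.89 and 0.87 with them set aside. These figures assume no treatment signal in affected children, an unchanged within-group SD, equal shares in the two arms and 24 per arm after dropout. The possible bias from perforation after randomisation matters more for interpretation, and its direction cannot be determined from the protocol.

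**What to change.** - Record drum status (intact, perforated, not seen) with each tympanogram. The third category is needed because otoscopy is conditional.
- Fix the analysed ear at baseline, choosing an affected ear with an intact drum where there is one, and keep it at all visits. Switching ears would make the change outcome compare two different ears.
- Class admittance from a perforated ear as not assessable, and report the counts by arm and visit.
- Treat perforation before and after randomisation differently. Setting ears aside on baseline status does not depend on treatment. Setting them aside on later status may, and counts by arm reveal that problem without removing it. So add a sensitivity analysis for ears that perforate after randomisation, for example counting them as unresolved, in addition to leaving them out.

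The cost is one extra CRF item, a few sentences of analysis rules, a few fewer readings and one extra sensitivity analysis. Eligibility and clinical care stay as they are.

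### Bare proportions from 60 children and about 30 controls are too imprecise to check the 35% and 42.5% planning figures; report both with 95% intervals (minor)

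*Protocol*

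**What the plan says.** Verifying the main-trial sample size is item 5 of the first objective (Protocol section 1.2) and a listed outcome in the registration data set. Section 2.2.4.1, under *The verification of sample size calculation for main study*, ties two planning figures to the main trial, for which "we plan to enrol 760 children in the main study":

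- Severe share: "We estimate that there will be 35% of the total sample of children with AOM in the severe group". The text then states: "Therefore, within this pilot study, we can assess the accuracy of this assumption".
- Control rate: the pilot will also check "the proportion in the control group with the resolution of pain at three days, which was 42.5" per cent.

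Section 2.4.3 sets the reporting: "we will report this outcome as the proportion of children in each stratum", together with the children in the control group who have pain at day 3. It names no interval, no tolerated deviation and no rule for reading the result. The next paragraph of that section does plan 95% confidence intervals, for the mean differences in the tympanometry sub-study.

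On size, the sample size section says "we will include 60 children with AOM in our pilot study". Section 2.1 randomises "with the allocation ratio of 1:1".

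**The concern.** Section 2.2.4.1 credits the pilot with an ability: to say whether two planning figures are accurate. That depends on precision, and the pilot was not sized for it. The sample size section says that no size was determined for the pilot as such; the 60 comes from the tympanometry comparison.

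A bare percentage hides how little 30 or 60 children can say. A proportion close to 42.5% could be taken as support for the 760 when the true rate is well away from it. A proportion that is off by chance could be taken as a reason to change the 760 when the planning figure was right. The concern is sampling error alone. It would remain even if setting, comparator and endpoint matched the main trial exactly.

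**Working it through.** **Inputs.** Severe share 35%, control resolution rate 42.5% and main-trial size 760 (section 2.2.4.1); pilot size 60 (sample size section); allocation 1:1 (section 2.1), hence about 60/2 = 30 controls. Section 2.4.3 counts children with pain rather than with resolution. If one is the complement of the other, the interval widths are the same.

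**The plan's own figures.** For the tympanometry comparison (SD 0.3, difference 0.3, power 0.9, alpha 0.05, taken as two-sided), n = 2(1.960 + 1.282)² × (0.3/0.3)² ≈ 21 per group by the normal approximation. The t-test correction gives 22, with power 0.8997. For dropout, 44/0.8 = 55, or 28 per group = 56. This agrees with "With a 20% allowance for dropouts, the total sample size becomes 56", which is then taken up to 60. The 760 cannot be reproduced: its target effect, power, alpha and dropout are not in the document.

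**Step 1: precision at the planning values.** Exact (Clopper-Pearson) limits for x out of n are the 0.025 quantile of Beta(x, n − x + 1) and the 0.975 quantile of Beta(x + 1, n − x).

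- Control rate, 13/30 = 43.3%: 25.5% to 62.6%.
- Severe share, 21/60 = 35%: 23.1% to 48.4%.

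Approximate half-widths, 1.96 × √(p(1 − p)/n), are 17.7 points for 42.5% with n = 30 and 12.1 points for 35% with n = 60. A half-width of 10 points needs 1.96² × 0.425 × 0.575/0.01 ≈ 94 controls, and 1.96² × 0.35 × 0.65/0.01 ≈ 88 children.

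**Step 2: chance that a 10-point error goes undetected.** The protocol gives no rule for agreement, so two plausible ones are tried. Each result is a binomial sum over the counts that pass.

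*Rule A: the exact 95% interval contains the planning figure.* With 30 controls, counts 8 to 18 pass (7/30 has upper limit 42.3%; 19/30 has lower limit 43.9%). With 60 children, counts 14 to 28 pass (13/60 has upper limit 34.2%; 29/60 has lower limit 35.2%).

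*Rule B: the point estimate is within 10 points.* Counts 10 to 15 of 30 pass, and counts 15 to 27 of 60.

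| Planning figure | True value | Rule A | Rule B |
|---|---|---|---|
| 42.5%, n = 30 | 32.5% | 80.8% | 51.5% |
| 42.5%, n = 30 | 52.5% | 84.2% | 45.2% |
| 35%, n = 60 | 25% | 66.5% | 54.9% |
| 35%, n = 60 | 45% | 65.2% | 55.3% |

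Wilson intervals give the same Rule A results. Wald intervals give 68.0% and 83.9% for the control rate, and 54.9% and 65.2% for the severe share. A tighter rule, within 5 points, gives 21% to 26% throughout.

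**Step 3: the opposite error.** If 42.5% is exactly right, counts 10 to 15 of 30 have total probability 73.1%. Under Rule B, a correct planning figure would therefore look wrong in 100 − 73.1 = 26.9% of pilots.

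**The case against.** **The protocol promises little.** It speaks of assessing and checking; it does not say that a result near 42.5% will be declared proof of the 760, or that any result triggers a resize. That stands, and it is why the point is minor. A reader might infer that the plan commits to a formal equivalence claim; the text does not go that far. It does claim an ability to judge accuracy, and the numbers do not support that.

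**Intervals for descriptive proportions are analysis-plan detail.** Section 2.4.3 also gives recruitment and compliance as plain percentages, and its 95% intervals belong to the between-group comparison, so this outcome was not singled out. This stands in part. Even so, the protocol states both the capability and the reporting method itself. The limited-sample caveat in section 2.2.4.1 covers only detection of treatment effects, not this check.

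**The detection figures depend on a rule the protocol lacks.** True. A reader might infer that a 10-point error would pass in two-thirds or more of pilots whichever figure is checked. That does not hold: the severe share gives 65% to 67% under Rule A, and Rule B gives 45% to 55%.

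**Dropout.** A reader might also cut the 30 controls to 24 by applying the 20% allowance. That allowance belongs to the tympanometry sub-study, which runs to day 90, while the control rate is read at day 3. The documents give no day-3 attrition figure, so 30 is used here.

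**No consequence for the 760 is shown.** This stands. As an illustration only, assume 80% power, two-sided 0.05, and 52.5% against 42.5%. Then n per arm = 7.849 × [p₁(1 − p₁) + p₂(1 − p₂)]/(p₂ − p₁)² = 388. At control rates of 25.5% and 62.6%, holding the 10-point difference fixed gives 329 and 340 per arm; holding the ratio fixed gives 885 and 148. The impact ranges from slight to large according to an effect scale that is not stated. The assumed case totals 776, not 760, so it is not the sponsor's calculation. Nor does the document say how the 35% share enters the 760.

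**Conclusion.** The concern holds as a minor point. At the planning values, the pilot's exact 95% intervals are about 25% to 63% for the control rate and 23% to 48% for the severe share. Data that imprecise cannot support the accuracy claim in section 2.2.4.1, and the reporting in section 2.4.3 would not show the imprecision.

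The interval widths rest only on 60 children, 1:1 allocation and binomial sampling, with no day-3 loss among about 30 controls. The detection rates (81% to 84% and 65% to 67%, or 45% to 55%) also depend on rules supplied here for illustration. It would be tempting to conclude that the 760 is wrong or that the main trial will be underpowered. The documents do not support that, because the main trial's target effect and power are not given.

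**What to change.** - In section 2.2.4.1, say that the pilot will estimate the two proportions with 95% confidence intervals, in place of assessing the accuracy of, or verifying, the planning figures. Align item 5 of section 1.2.
- In section 2.4.3, report the severe share and the control-group day-3 proportion with exact 95% confidence intervals. Using the sponsor's own main-trial inputs, show the main-trial sample size across the interval for the control rate.
- State that an interval containing the planning figure will be described as compatible with it, not as verifying it.

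This does not make the pilot more able to detect a wrong planning figure; it stops the report from implying an ability that the pilot lacks. The cost is wording, two intervals and a short recalculation, with no added children, visits or procedures. The sponsor gives up the claim that 60 children verify the 760.
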